## Abstract

**Background:** Burgeoning pre-clinical evidence suggests that therapeutic targeting of glycogen synthase kinase 3β (GSK3β), a convergence point of multiple cellular protective signaling pathways, confers a beneficial effect on acute kidney injury (AKI) in experimental models. However, it remains unknown if GSK3β inhibition likewise mitigates AKI in humans. Cardiac surgery associated acute kidney injury (CSA-AKI) poses a significant challenge for clinicians and currently the only treatment available is general supportive measures. Lithium, an FDA approved mood stabilizer, is the best-known GSK3β inhibitor and has been safely used for over half a century as the first line regimen to treat bipolar affective disorders. This study attempts to examine the effectiveness of short term low dose lithium on CSA-AKI in human patients.

**Methods/Design:** This is a single center, prospective, randomized, double blinded, placebo controlled pilot study on patients undergoing cardiac surgery with cardiopulmonary bypass. Patients will be randomized to receive a small dose of lithium or placebo treatment for three consecutive days. Renal function will be measured via creatinine as well as novel AKI biomarkers. The primary outcome is incidence of AKI according to Acute Kidney Injury Network (AKIN) criteria, and secondary outcomes include receipt of new dialysis, days on dialysis, days on mechanical ventilation, infections within 1 month of surgery, and death within 90 days of surgery.

**Discussion:** As a standard selective inhibitor of GSK3β, lithium has been shown to exert a beneficial effect on tissue repair and regeneration upon acute injury in multiple organ systems, including the central nervous system and hematopoietic system. In experimental AKI, lithium at small doses is able to ameliorate AKI and promote kidney repair. Successful completion of this study will help to assess the effectiveness of lithium in CSA-AKI and could potentially pave the way for large-scale randomized trials to thoroughly evaluate the efficacy of this novel regimen for preventing AKI after cardiac surgery.

**Trial Registration:** This study was registered prospectively on the 17th February 2017 at ClinicalTrials.gov (NCT03056248, https://clinicaltrials.gov/ct2/show/NCT03056248?term=NCT03056248&draw=2&rank=1).

## Introduction

Cardiac surgery-associated acute kidney injury (CSA-AKI) is a significant problem. The prevalence varies from 0.3 to 22.9% depending on the definition of acute kidney injury (AKI) (1). In a study of 2,222 patients undergoing elective cardiopulmonary bypass (CPB) surgery with or without valvular surgery, 7.7% had AKI, and 1.4% required dialysis (2). Another prospective study by Ostermann et al. of 2,337 patients undergoing cardiac surgery, 2.7% needed continuous renal replacement therapy (3). The etiopathogenesis of AKI in this population is multifactorial (4). Factors associated with AKI in such patients include patient comorbids, procedure related factors, exogenous nephrotoxic agents, hemodynamic insults and genetic factors (5). Mechanism of AKI includes increased afferent arteriolar vasoconstriction leading to ischemic injury. In addition, CPB induces a proinflammatory state, intravascular hemolysis and hemoglobinuria. Although pulsatile flow overall has improved inflammatory response due to reduced leukocyte adherence, in some studies there is no difference in AKI incidence (6). In the initial course the kidney function may still be intact. However, if there is prolonged ischemic, oxidative, and inflammatory injury, further damage will occur leading to renal tubular cell disruption.

CSA-AKI has significant clinical consequences. It is an independent predictor of mortality, morbidity, increased length of hospitalization and costs (7, 8). In a study of over thirty-one thousand patients it was found that a reduction of glomerular filtration rate beyond 30% was associated with 4 times the mortality risk (9). Another retrospective study by Thakar et al. showed that incidence of infections after cardiac surgery was 1.6% in patients without renal failure, 23.7% in patients with renal failure not requiring dialysis, and 58.5% in patients with renal failure requiring dialysis (10). Moreover, these patients were also at increased risk of end stage renal disease in the future (11–13). In another study where AKI was classified according to RIFLE criteria, it was found that survival post cardiac surgery was associated with varying stages of AKI, with 51% at the risk of AKI, 42% having kidney injury, and 26% having kidney failure (14).

Various pharmacologic approaches have been tried in hope of preventing early CSA-AKI, including diuretics, vasodilators, and anti-inflammatory drugs. For instance, nesiritide was studied in a retrospective cohort study in adult non-transplant cardiac surgery patients. It showed reduction in dialysis and death with no statistical significance (15). In a prospective study fenoldopam and N-acetylcysteine were found to improve creatinine clearance by 6.5 and 7.5 ml, respectively, with no change in length of stay in hospital or intensive care unit (16). However, other studies have shown contrary results (17, 18). Sodium bicarbonate, statins and mannitol have been tried but did not demonstrate consistent and significant effects on improvement of AKI (19, 20). The above mentioned therapeutic preventive strategies lack high quality evidence to support their use and are not standard of care (21). Thus, the current best therapy for CSA-AKI is still limited to optimizing patient hemodynamics, supportive care, and renal replacement therapy when indicated (22, 23).

AKI in this setting is thus an extremely complex process involving multiple pathophysiologic pathways, among which glycogen synthase kinase 3β (GSK3β) has emerged as a key factor mediating the pathogenesis of AKI. As a highly conserved serine/threonine protein kinase that is ubiquitously expressed, GSK3β was originally found in early 1980s to be a pivotal transducer of the insulin signaling pathway *via* phosphorylating glycogen synthase and thereby regulating glucose metabolism and the biogenesis of glycogen (24, 25). But recently, a growing body of evidence suggests that GSK3β is also centrally involved in a large number of other cellular signaling pathways, including Wnt/β-catenin, NFκB, CREB pathways and cytoskeleton regulation (26, 27). Of the many signaling cascades, GSK3β is situated at the nexus of the reperfusion injury salvage kinase pathway (involving PI3K/Akt signaling) and the survivor activating factor enhancement pathway (involving JAK/STAT3 signaling) and thus become a convergence point of protective signaling (28, 29). In concordance, GSK3β has been implicated in organ injury, repair and regeneration. Therapeutic targeting of GSK3β has demonstrated a potent beneficial action in numerous animal models of acute organ injury, including AKI (Figure 1). While the highly selective small molecule inhibitors of GSK3β have exhibited promising therapeutic effects in pre-clinical studies, they may take years or even decades to go through human trials and be approved for use in patients (30).

**Figure 1 F1:**
[figure not shown]
Schematic diagram depicting pathways leading to cardiovascular surgery-associated acute kidney injury (CSA-AKI) and role of GSK3β in the pathogenesis. There are multiple, complicated pathways mediating CSA-AKI. Cardiovascular surgery is a state of low blood flow, there is hypothermia, blood loss, activation of renin angiotensin aldosterone system (RAAS). Additionally due to CPB there is hemolysis, systemic inflammatory response syndrome (SIRS) and microemboli formation. Together these lead to reduced renal perfusion, ischemia, increase in oxidative and inflammatory injury, which in turn overactivate GSK3β. GSK3β increases proinflammatory NFκB activation, potentiates mitochondrial dysfunction as well as impairs Nrf2 antioxidant response, culminating in CSA-AKI. As an FDA-approved mood stabilizer, lithium is a standard and effective inhibitor of GSK3β and is able to ameliorate diverse types of AKI in pre-clinical models. Its efficacy in preventing CSA-AKI will be tested by this prospective, randomized, double blinded, placebo-controlled pilot clinical trial.

Luckily, there are some Food and Drug Administration (FDA)-approved drugs with GSK3β inhibitory activities. Lithium is the best-known inhibitor of GSK3β and has been used as standard selective inhibitor of GSK3β for basic science research for decades. In addition, lithium is a US FDA–approved mood stabilizer, which has been used for nearly seven decades as first line agent to treat bipolar affective disorders in adults and children (31, 32). Indeed, lithium has shown powerful protective effect on a multitude of models of acute organ injury, including AKI, and this beneficial action has been attributable to GSK3β inhibition, which subsequently prevents cellular apoptosis and promotes cellular repair and repopulation (see **Figure 3**). It has been shown to have a positive effect on tissue repair and regeneration in both the central nervous system and hematopoietic system. It causes leukocytosis (33) and increased gray matter in humans (34). In a study by Bao et al. in mouse models of cisplatin as well as ischemia/reperfusion-induced AKI, there was a reduction in serum creatinine (SCr) in lithium treated mice as compared to controls. Lithium was found to promote repair of tubular cells hence improvement of AKI in murine model (35). Moreover, low dose lithium also has a demonstrable anti-proteinuric and renal regenerative effect (36).

In this context, since lithium inhibing GSK3β, has shown to promote renal tubular epithelial survival and recovery of kidney function in pre-clinical studies (35), it is tempting to speculate that therapeutic targeting of GSK3β by short term low dose lithium treatment may protect against AKI in man. This pilot study aims to explore this property of lithium in patients with CSA-AKI. There is a dire need of an efficacious pharmacotherapy in the area of AKI. Successful completion of this study may pave the way to establish a novel therapeutic strategy to reduce the incidence of CSA-AKI.

## Methods

### Study Design

The Lithium in cardiac surgery-associated acute kidney injury (LiCS-AKI) study aims to determine if low dose lithium will impact renal function in patients undergoing elective cardiac surgery requiring CPB. The study is designed as a single center, prospective, randomized, control study where patients undergoing cardiac surgery requiring CPB will be randomized into two groups, namely intervention and placebo groups. The intervention group will receive low-dose oral lithium treatment on three consecutive days while the placebo group will get placebo for the same number of days. As AKI rates are lower in cardiovascular surgery without CPB (37), inclusion of patients without CPB will thus add a confounding variable in the interpretation of data. To overcome this variable, much larger sample sizes of patients would be required. As such, patients undergoing cardiac surgery without CPB will not be included.

### Study Setting

The study will take place in adult inpatient units, including telemetry, regular floor, intensive care units, coronary care units as well as outpatient cardiothoracic clinics. Patients will be identified by chart review and referral from cardiothoracic team. They will be explained about the study and informed consent will be taken. There is no financial compensation for the patients and there will be no advertisement regarding the study.

### Intervention

The study intervention is the addition of lithium carbonate for 3 days in addition to usual best practice for perioperative cardiothoracic surgery patients (Figures 2, 3). This is an investigator lead trial without industry input. In brief, the consenting patients will take placebo or small dose lithium carbonate (300 mg) (38) orally on the day of surgery and then two more doses every 24 h. This dose of lithium carbonate is only 1/3 to 1/4 of the standard dose for psychiatric disorders (39). This dose was determined based on a number of pre-clinical studies, which suggest that microdose lithium that is one-third to one-fourth of the neurobiological dose is sufficient to block GSK3β in the diseased kidney and prevent AKI in animal models (36). Blood will be drawn on postoperative day 1 of the surgery and urine samples will be collected on postoperative day 0, 1, 2 and 3. Therapeutic drug monitoring of lithium will be done for 2 days to ensure that the blood concentration of lithium is within therapeutic range. The therapeutic range will be 0.6 to 0.8 meq/L (32, 40). As per standard of care, therapeutic drug monitoring of lithium will be initiated 24 h after the first dose (41).

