**Figure 3 F3:**
[figure not shown]
Scheme diagram depicting study interventions to be given in this trial. Patients will receive microdose lithium carbonate or placebo treatment on day 0, 1, and 2 after the cardiovascular surgery. *Biomarkers that will be sent include urinary NGAL, KIM1, tissue inhibitor of metalloproteinases-2 (TIMP-2), and insulin-like growth factor-binding protein 7 (IGFBP-7).

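### The 0.6 meq/L floor of the lithium monitoring range does not fit a fixed 300 mg once-daily, three-dose regimen and should become an upper safety limit only

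*Protocol article*

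**What the plan says.** All of the following is in the protocol article.

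- **Dose and schedule** (Methods, Intervention): 300 mg lithium carbonate "orally on the day of surgery and then two more doses every 24 h". The Figure 3 legend agrees: "Patients will receive microdose lithium carbonate or placebo treatment on day 0, 1, and 2 after the cardiovascular surgery".
- **Dose relative to psychiatric use** (Intervention): "This dose of lithium carbonate is only 1/3 to 1/4 of the standard dose for psychiatric disorders". The reason given is that "microdose lithium that is one-third to one-fourth of the neurobiological dose is sufficient to block GSK3β in the diseased kidney".
- **Monitoring** (Intervention): "Therapeutic drug monitoring of lithium will be done for 2 days to ensure that the blood concentration of lithium is within therapeutic range". The next sentence reads "The therapeutic range will be 0.6 to 0.8 meq/L (32, 40". On timing, "therapeutic drug monitoring of lithium will be initiated 24 h after the first dose".
- **Source of the range**: one of its two references, number 32, is also cited in the Introduction for lithium "as first line agent to treat bipolar affective disorders in adults and children (31, 32".
- **Purpose of monitoring elsewhere** (Safety Monitoring and Risk to Subjects): serum levels are monitored for safety and go to an independent clinician.
- **Why psychiatric doses are high** (Discussion): a very high dose is needed to act in the brain, and the kidney-protective dose is still unknown.

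**The concern.** One section pairs a dose chosen to be a fraction of the psychiatric dose with a two-sided concentration range that appears to come from psychiatric use. The text says that monitoring is meant to ensure this range. A regimen that aims below psychiatric exposure should not be expected to produce psychiatric levels, least of all after only one or two doses.

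What is at stake is the meaning of the monitoring threshold. If most lithium patients sit below 0.6, the lower bound tells the independent monitor nothing. It also misleads anyone planning the follow-on trial about the exposure being studied. And it gives the same measurement a target-attainment purpose under Intervention and a safety purpose under Safety Monitoring.

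**Working it through.** The article shows no calculation behind 0.6 to 0.8 meq/L, so there is no derivation to reproduce. Two independent checks follow.

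**Check 1: the article's own dose ratio.** Inputs from Intervention: trial dose = 1/3 to 1/4 of the standard dose; range 0.6 to 0.8 meq/L. Assumptions not in the article: the standard dose yields 0.6 to 0.8, and level is proportional to dose.

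- Lowest: 0.6 / 4 = 0.15 meq/L. Highest: 0.8 / 3 = 0.27 meq/L.
- In reverse, for 300 mg to yield 0.6 the standard dose would have to yield 0.6 × 3 = 1.8 to 0.6 × 4 = 2.4 meq/L.

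This is a steady-state scaling. A three-dose course would not be expected to exceed the steady state of the same daily dose.

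**Check 2: one-compartment model with full, instantaneous absorption.** Input from the article: 300 mg at 0, 24 and 48 h. Assumed: distribution volume V of 25 to 90 L, half-life of 12 to 48 h, and samples taken just before the next dose. The article does not say they are pre-dose.

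- Lithium per dose: 300 / 73.89 × 2 = 8.12 meq (molar mass of lithium carbonate 73.89, two lithium ions per unit).
- Fraction left after 24 h: f = 0.5^(24 / half-life).
- Before dose 2 (24 h): 8.12/V × f.
- Before dose 3 (48 h): 8.12/V × (f + f²).
- Just after dose 3: 8.12/V × (1 + f + f²).

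| V (L) | Half-life (h) | 24 h pre-dose | 48 h pre-dose | Just after dose 3 |
|---|---|---|---|---|
| 90 | 12 | 0.02 | 0.03 | 0.12 |
| 49 | 12 | 0.04 | 0.05 | 0.22 |
| 49 | 24 | 0.08 | 0.12 | 0.29 |
| 49 | 36 | 0.10 | 0.17 | 0.34 |
| 30 | 36 | 0.17 | 0.28 | 0.55 |
| 25 | 36 | 0.20 | 0.33 | 0.66 |
| 25 | 48 | 0.23 | 0.39 | 0.72 |
| 30 | 60 (beyond the range) | 0.21 | 0.36 | 0.63 |

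Over the assumed ranges the pre-dose levels run from 0.02 to 0.23 meq/L at 24 h and from 0.03 to 0.39 at 48 h. None reaches 0.6.

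**Sensitivity to sampling time.** A sample taken just after dose 2 would be at most 8.12/25 × (1 + 0.707) = 0.55 meq/L, still below the floor. Just after dose 3, the floor is exceeded at the small-volume, slow-clearance end of the table.

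**Limit with no elimination at all.** Reaching 0.6 needs V of at most 8.12/0.6 = 13.5 L after one dose, 16.24/0.6 = 27.1 L after two and 24.36/0.6 = 40.6 L after three. At V = 25 L the 48 h pre-dose level could therefore pass 0.6 if clearance stopped (16.24/25 = 0.65), but not at any half-life in the assumed range.

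**The case against.** The strongest reply is that the lower bound has no operational effect. The regimen is the same wherever it is described, no section provides for titration, and no action is attached to a low level. Safety Monitoring says what the levels are for, and for that purpose 0.8 works as a ceiling. All of this stands. It limits the consequence, but it does not make the sentence in Intervention correct: that sentence names a two-sided range and says monitoring will ensure it.

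A second reply is that the psychiatric origin of the range is an inference. That also stands. Reference 32 is shared with the statement on bipolar treatment, but neither source is visible. The kinetic check does not depend on where the range came from.

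A third reply is that the pharmacokinetic inputs are assumptions and that patients who develop AKI may clear lithium slowly; eGFR above 60 is required only at entry. This is why the table extends to slow half-lives. It changes the picture after the third dose, but not at the 24 h and 48 h pre-dose checks.

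Three stronger readings are tempting, and the documents do not support them.

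- A reader might infer that the trial would raise the dose to about 900 to 1,200 mg a day (3 to 4 × 300 mg) to meet the range. Nothing in the article provides for that, and the microdose rationale argues against it.
- A reader might infer that 0.6 can never be reached, or only with no elimination. The table shows peaks of 0.63 to 0.72 after the third dose with finite elimination.
- A reader might count the lack of a dose-holding rule or of a sampling time relative to dose as a defect. A journal article may leave such details to the full protocol.

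**Conclusion.** The point holds as a minor error of specification. The 0.6 meq/L floor is wrong for the stated regimen. Expected levels at the 24 h and 48 h pre-dose checks are about 0.15 to 0.27 meq/L by dose proportionality, and about 0.02 to 0.39 meq/L under the assumed kinetics.

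The first estimate rests on the standard dose yielding 0.6 to 0.8 meq/L. The second rests on V of 25 to 90 L, half-lives of 12 to 48 h and pre-dose sampling. None of these is given in the article, but the two checks agree.

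The floor conflicts with the microdose argument under Intervention and in the Discussion, and it has no part in the safety purpose. The 0.8 upper bound is not in dispute. The dose, sample size, error rate and primary analysis are untouched.

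**What to change.** In Intervention, delete the 0.6 floor and the words about ensuring a therapeutic range. Replace them with wording such as: *Serum lithium is measured for 2 days, starting 24 h after the first dose. The independent monitor reviews the results against an upper safety limit of 0.8 meq/L. The 300 mg dose is not raised for a low level.*

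This aligns Intervention with Safety Monitoring and with the microdose rationale. The cost is an amendment of two or three sentences, with no added tests, visits or patients.

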**Figure 2 F2:**
[figure not shown]
Flow diagram depicting the design of this single center, randomized, double blinded, placebo controlled pilot trial. Patients scheduled to undergo cardiovascular surgeries with cardiopulmonary bypass (CPB) will be subjected to eligibility assessment for inclusion in this trial to test the potential of short-term use of microdose lithium for protecting against CSA-AKI. This will include patients in the emergency department, general floors, critical care units, coronary care unit and step down/ telemetry units.

**Figure 3 F3:**
[figure not shown]
Scheme diagram depicting study interventions to be given in this trial. Patients will receive microdose lithium carbonate or placebo treatment on day 0, 1, and 2 after the cardiovascular surgery. *Biomarkers that will be sent include urinary NGAL, KIM1, tissue inhibitor of metalloproteinases-2 (TIMP-2), and insulin-like growth factor-binding protein 7 (IGFBP-7).

### Study Population

#### Eligibility Criteria

The inclusion criteria for this trial are as follows: both men and women, 18 years and older, will undergo elective cardiovascular procedure such as aortic valve surgery, mitral valve surgery, coronary artery bypass grafting, or any combination of the above procedures. The subjects must have stable renal function with eGFR > 60 ml/min/1.73 m^2^ and creatinine change <0.3 mg/dl in the preceding 1 month prior to scheduled surgery.

The exclusion criteria for this trial are as follows: subjects who

Have ejection fraction of <20% prior to surgeryHave estimated glomerular filtration rate <15 ml/min/1.73 m2 as calculated by Chronic Kidney Disease Epidemiology Collaboration (CKD-EPI) formulaWill have cardiac surgery performed without using cardiopulmonary bypassHave ongoing sepsis or history of sepsis in the last 2 weeks, defined as having 2 of the following criteria: body temperature >38°C or <36°C, pulse rate >90/min, RR >20/min, WBC >12 or >10% polymorphonuclear cells plus a documented sourceHave documented rise in creatinine ≥ 0.3 mg/dl in the preceding 1 month prior to surgeryHave been deemed to have AKI at the time of the surgery by treating clinicianAre on acute or chronic maintenance dialysis at the time of randomizationHave AKI due to glomerulonephritis, thrombotic microscopic angiopathy, obstructive nephropathy, interstitial nephritisAre taking lithium for any conditionsUnable to absorb lithium or take any medications orally.

### Study Endpoints

The primary endpoint of AKI is a composite of the occurrence of any of the following at 1-week from surgery: AKI based on the Acute Kidney Injury Network (AKIN) criteria. Other components include new onset dialysis at 30 or 90 days from surgery, and death within 90 days in lithium treated patients matched with controls.

Secondary endpoints of renal function/injury, post-operative therapy and infection will be monitored during the patient's hospital stay. Measures of renal function/injury include SCr, albumin to creatinine ratio, estimated glomerular filtration rate (eGFR), and urinary and urinary biomarkers; additionally, the number of days on renal replacement therapy (RRT), days on post-surgical mechanical ventilation, and infection will also be assessed as secondary outcomes.

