### Statistical Analysis

This randomized two-arm study is designed to test the null hypothesis of no difference in the primary endpoint of incidence of AKI as defined by AKIN criteria between the two treatment arms, placebo-control and lithium treatment. The primary endpoint will be analyzed on an intention-to-treat basis and patients will therefore be analyzed according to the assigned treatment group at study enrollment. The hypothesis of the study is based on the proportional incidence of AKI as follows:

$$\begin{array}{l} {\text{H}}_{\text{o}}:\lambda_{\text{lithium}}=\;\lambda_{\text{control}}\\ {\text{H}}_{\text{a}}:\lambda_{\text{lithium}}<\;\lambda_{\text{control}} \end{array}$$

Descriptive statistics and exploratory data analysis will be undertaken to summarize baseline characteristics between the control group and the lithium treated group to determine homogeneity and to identify potential differences that might be associated with incidence of AKI. Continuous data will be tested for goodness-of-fit to the normal distribution using Shapiro-Wilk test. If not normally distributed, the log-transformation of the data will be assessed for normality. Continuous data will be expressed as mean ± standard deviation (SD) of the untransformed or log-transformed version, or if neither are normally distributed, as median with interquartile range. Categorical data will be presented as frequency and percent. Comparisons of continuous data will be evaluated using two-sample *t*-tests or Wilcoxan rank sum test. For categorical variables, the chi-square test or, if frequencies are low (≤ 5), Fisher exact test will be used to compare groups. Statistical significance is defined as a *p*-value < 0.05.

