To examine the primary endpoint and test the study hypothesis for the effect of lithium on the incidence of AKI, contingency table analysis using chi-square will compare the proportion of AKI within the respective treatment groups. A predictive model that identifies baseline characteristics, including treatment assignment, associated with risk of AKI will be developed. Multivariate testing will use linear regression for continuous outcomes and logistic regression for dichotomous outcomes. Analysis comparing the placebo-control and lithium groups on each baseline characteristic, one at a time, using ANOVA with adjustment for age and sex will be performed. An adjusted logistic regression model based on the dichotomous outcome of occurrence or not of AKI will be further developed to identify characteristics significantly related to AKI. Composite endpoint events, consisting of the first occurrence of AKI, new onset dialysis, and cardiovascular/all-cause mortality, will be compared between treatment groups. Using appropriate uni- and multivariate methods, secondary outcome measures will be incorporated including assessments of renal function/injury such as SCr, NAGL, KIM1, urine TIMP-2, IGFBP7 and [TIMP-2] × [IGFBP-7], urine albumin Cr ratio, as well as indicators of post-operative course including days on mechanical ventilation, days on RRT and infection.

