Stepwise multivariate linear regression analysis will be utilized to examine the independent predictors of changes in renal function over time. The longitudinal effect of lithium on kidney function will be estimated by applying generalized linear mixed model with time (continuous variable) as a random coefficient. The percent change in SCr, NAGL, KIM1, urine TIMP-2, IGFBP7 and [TIMP-2] × [IGFBP-7], and urine albumin Cr ratio at 1 week, 30 days and 60 days will be evaluated. Other covariates identified by univariate analysis or by stepwise selection with Akike information criteria will be included in the model. Additionally, risk factors such as age, diabetes, history of chronic kidney disease (CKD) and dialysis, duration of CPB, aortic cross clamp time, type of surgery (emergent vs. elective), valvular vs. non-valvular and duration of surgery will be examined. All multivariate models will be tested for interaction among predictors. Due to the problem of multiple comparisons, the multivariate modeling will be cautiously interpreted and inference will be regarded as limited, but will be examined for possible hypothesis-generating evidence owing to the multifactorial nature of CSA-AKI.

The primary endpoint is based on the first occurrence within 1 week from surgery of AKI and other composite events described above, therefore time-to-event analysis is limited in assessing risk due to the 1-week AKI criteria from exposure at time of surgery. The hazard associated with outcomes outside of the 1-week threshold, such as death and new onset dialysis, will be examined using time-to-event analysis. The predicted probability of the binary occurrence of these endpoints will be calculated using logistic regression with adjustment for age, sex, and baseline renal function measures. Model performance will be summarized using receiver operating characteristic analysis. Time-to-event for the mortality and dialysis endpoints will be examined using Kaplan-Meier analysis with log-rank estimates to compare the lithium and control groups. Hazard ratios will be calculated using Cox proportional-hazard model adjusted as described above. Model diagnostics using Cox-Snell residual plots for goodness-of-fit, and the null hypothesis of proportional hazard assumption will be tested. The extended Cox model will be used to test for interaction among predictors and time.

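### The primary endpoint is stated inconsistently: AKI alone in the hypothesis, primary test and sample size, but a composite with 90-day dialysis and death in Study Endpoints

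*Protocol article*

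**What the plan says.** **AKI alone.** The Abstract states: "The primary outcome is incidence of AKI according to Acute Kidney Injury Network (AKIN) criteria". It lists dialysis and death as secondary: "secondary outcomes include receipt of new dialysis, days on dialysis, days on mechanical ventilation", and then "infections within 1 month of surgery, and death within 90 days of surgery". The first paragraph of Statistical Analysis sets the null hypothesis as "no difference in the primary endpoint of incidence of AKI as defined by AKIN criteria between the two treatment arms". The second paragraph tests the proportion with AKI by chi-square. Renal Function Measurement sets the window at 1 week from surgery. Sample Size Estimation uses an AKI rate of about 20%.

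**A composite running to 90 days.** Study Endpoints calls the primary a composite assessed at 1 week and names AKI as its only item at that time. It then continues: "Other components include new onset dialysis at 30 or 90 days from surgery, and death within 90 days".

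**A composite with a 1-week reference.** The last paragraph of Statistical Analysis says: "The primary endpoint is based on the first occurrence within 1 week from surgery of AKI and other composite events described above". The next sentence places death and new dialysis beyond the 1-week threshold and assigns them to time-to-event analysis.

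**A composite without a window.** The second paragraph of Statistical Analysis also compares "Composite endpoint events, consisting of the first occurrence of AKI, new onset dialysis, and cardiovascular/all-cause mortality".

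**Follow-up.** Data Collection takes chart data up to 60 days after surgery. The only later contact is a 6-month clinic visit, for which Table 1 lists serum chemistry and eGFR.

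**The concern.** The choice of primary endpoint decides which patients count as events in the result that matters most. Here new dialysis and death are components of the primary endpoint in one section and secondary outcomes in another. Dialysis carries two alternative time points. Mortality is written as cardiovascular and all-cause together, which are two different endpoints.

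The sections can therefore give different primary results from the same data, and nothing in the article says which section governs. The sponsor could settle the matter after seeing the outcome. That matters even in a pilot: Sample Size Estimation and the Discussion both make the decision to move to a larger trial depend on evidence of efficacy.

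**Working it through.** **Step 1. Classify the same patient under each definition.**

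| Patient | AKI alone (Abstract, hypothesis, chi-square) | Study Endpoints composite | Last paragraph of Statistical Analysis, if the week covers every component |
|---|---|---|---|
| AKI in week 1 | event | event | event |
| Death in week 1, no AKI | non-event | event | event |
| Death on day 40, no AKI | non-event | event | non-event |
| First dialysis after day 30 and by day 90, no week-1 AKI | non-event | depends on whether 30 or 90 days is used | non-event |

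If the week in that last paragraph limits only AKI, the third column no longer describes a separate endpoint and the paragraph points back to the Study Endpoints composite. The first two columns conflict on either reading.

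**Step 2. Find which event was sized.** The inputs from Sample Size Estimation are a 20% rate, a 25% relative reduction (0.25 × 20 = 5 points), a one-sided 80% limit (z = 0.8416) and 91 per arm. The formula is

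n per arm = z² × [p₁(1 − p₁) + p₂(1 − p₂)] / 0.05².

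- 20% in both arms: 0.8416² × 0.32 / 0.0025 = 90.67, rounded up to 91 per arm and 182 in total. This matches the stated figure.
- 20% against 15%: 81.46, so 82 per arm and 164 in total. No match.
- 17.5% in both arms: 81.81, so 82 per arm. No match.

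Of the inputs tried, only 20% in both arms returns 182, and the article attaches that 20% to AKI. The half-width at 91 per arm is 0.8416 × √(0.32/91) = 4.99 points.

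**Step 3. See what a composite would change.** The article gives no rate for dialysis or death by day 90 among patients without week-1 AKI, so the added rate below is an assumption.

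- Patients whose primary status differs between AKI alone and the 90-day composite: 182 × 0.01 = 1.8 to 182 × 0.05 = 9.1, about 2 to 9, if 1 to 5 points are added.
- Half-width at 22% in both arms: 0.8416 × √(2 × 0.22 × 0.78/91) = 5.17 points.
- Half-width at 22% against 16.5% (the same 25% reduction): 0.8416 × √((0.1716 + 0.1378)/91) = 4.91 points.
- Number needed for a fixed 5-point margin with equal arms: 190 at 21%, 196 at 22%, 214 at 25%.

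**Step 4. Compare component windows with follow-up.** Death and dialysis are to be counted to day 90, but chart data stop at day 60. As described, events from day 61 to day 90 have no stated source.

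**The case against.** The strongest reply is that the confirmatory route is coherent. The hypothesis, chi-square test, 1-week window and sample size all use AKI, and the composite appears in Statistical Analysis as a separate comparison. The trial was also registered prospectively, and the record, which cannot be seen here, may settle the choice. This has weight: it shows which endpoint should be kept, and it limits how far one can say the choice is truly open. It does not remove the contradiction, because the section headed Study Endpoints says something else. Nor is this condensation in a journal article: condensing leaves things out, whereas these are positive statements that disagree.

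Two stronger readings are tempting.

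- A reader might infer three clearly separate primary endpoints. The last paragraph of Statistical Analysis does not support that. Its 1-week limit may attach to AKI only, since the next sentence puts death and dialysis beyond it. It is ambiguous wording that needs correcting.
- A reader might infer that a composite would make 182 patients too few. That requires an assumed higher rate, equal rates in both arms and a margin frozen at 5 points. With a 25% reduction from 22%, the half-width is 4.91 points and the 5-point property holds. If the margin is rescaled as 25% of 22%, it becomes 5.5 points, above even the equal-arms limit of 5.17.

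**Conclusion.** The contradiction stands and should be corrected before analysis. The firm conflict is between AKI alone (Abstract, hypothesis, chi-square test and sizing) and the 90-day composite in Study Endpoints. The last paragraph of Statistical Analysis adds ambiguity, and the composite's dialysis time point and mortality definition are left open.

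The consequence is that the primary result can differ between sections, not that it must. The number of discordant patients is probably small: patients dialysed soon after surgery would mostly already count as AKI, and the only dialysis rates in the Introduction are 1.4% and 2.7%. The range of about 2 to 9 of 182 rests wholly on the assumed 1 to 5 points. The effect on precision is minor and depends on the assumptions in Step 3. The case for change rests on removing a possible post-hoc choice of primary endpoint.

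**What to change.** 1. Name one primary endpoint, AKIN AKI within 7 days of surgery, which is the event tested and sized. Use it in the Abstract, Study Endpoints, every paragraph of Statistical Analysis that mentions the primary, and Sample Size Estimation.
2. State how a death within 7 days without AKI is counted, for example with a sensitivity analysis that scores it as an event. Building early death or dialysis into the primary itself would define a different event from the one sized at 20%.
3. Make the composite of AKI, new dialysis and all-cause death secondary, with one time point in place of the two now given for dialysis and one mortality definition.
4. Reconcile that time point with Data Collection: either extend collection of dialysis and vital status to 90 days, or set the composite at a day within 60.

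The cost is protocol wording and a check against the registry entry, plus a short extension of chart follow-up if 90 days is kept. The sample size does not need to change.
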